### Outcome measures

2.5

#### Primary outcomes

2.5.1

The primary outcome is the between-group difference change in 6MWD from baseline (T0) to Week 6 (T6). The 6MWD measurements collected weekly during the intervention period (T1–T6) will be used in supportive longitudinal data to describe the trajectory of efficacy over time, but will not serve as an additional confirmatory primary endpoint.

The 6-Minute Walk Test will be conducted according to American Thoracic Society (ATS) guidelines (16). The test will be performed on a 30-meter straight, hard-surfaced corridor, with the start and turn points marked by cone markers. Before testing, patients rest near the starting point for at least 10 min. During the test, participants will be instructed to walk as far as possible within 6 min, and slow down, stop, or rest as needed. Standardized encouragement will be provided every minute. The total distance walked within 6 min will be recorded. The modified Borg dyspnea scale will be assessed immediately before and after each test. All tests will be conducted by evaluators who have undergone standardized training, following a standardized protocol.

#### Key secondary outcomes

2.5.2

Key secondary outcomes include: (1) dyspnea severity, assessed using the mMRC scale and modified Borg dyspnea scale; (2) respiratory health status, assessed using the CAT scale; (3) pulmonary function, including forced expiratory volume in 1 s (FEV_1_), forced vital capacity (FVC), and the FEV_1_/FVC ratio; and (4) adherence-related outcomes, including attendance rate and completion rate.

#### Exploratory outcomes

2.5.3

Exploratory outcomes include: (1) arterial blood gas parameters, including partial pressure of arterial oxygen (PaO_2_) and partial pressure of arterial carbon dioxide (PaCO_2_); (2) Traditional Chinese Medicine (TCM) syndrome assessment, assessed using the TCM Syndrome Scale; (3) patient satisfaction; (4) safety: assessed by adverse event records; and (5) long-term follow-up outcome, defined as the number of acute exacerbations of COPD (AECOPD) episodes during the 1-year post-intervention follow-up period.

All non-primary outcome measures will be analyzed as secondary or exploratory outcome measures and interpreted with caution.

### Data collection and management

2.6

All data are collected in the Case Report Forms (CRFs). Evaluators responsible for questionnaires and testing possessed relevant practical experience. To ensure rigorous data collection, this study will train evaluators to standardize testing principles, standardized prompts, and outcome recording protocols. To minimize measurement error, each indicator test for every subject will be administered by the same evaluator.

A unified Electronic Data Collection System (EDC) will be established. Before entering data into the EDC, all CRFs will be reviewed for errors and missing data. All data will undergo thorough verification before export to relevant statistical software. Access will be restricted to researchers and authorized personnel only.

### Statistical analysis

2.7

All statistical analyses will be conducted in accordance with the pre-specified statistical analysis plan. The primary non-inferiority analysis will be performed simultaneously in both the intention-to-treat (ITT) and per-protocol (PP) populations.

The primary endpoint is the between-group difference change in 6MWD from baseline to week 6 (T6). The treatment effect difference will be defined as the mean change in 6MWD in the MTG minus that in the CPRG. The primary endpoint will be analyzed using a mixed model for repeated measures (MMRM), which will serve as the main confirmatory analytic approach. The model will incorporate 6MWD measurements at all pre-specified follow-up time points. Treatment group, visit time, the interaction term between group and time, study center, and baseline 6MWD will be treated as fixed effects. And an appropriate covariance structure will be used to account for the correlation of repeated measurements within participants.

Non-inferiority will be assessed based on the between-group difference in change from baseline in 6MWD at T6, as estimated by this model. If the lower limit of the two-sided 95% confidence interval for the treatment effect difference is greater than the pre-specified non-inferiority margin of −25 m, the music therapy group will be deemed non-inferior to the conventional pulmonary rehabilitation group.

Weekly repeated 6MWD measurements will also be used to support longitudinal analyses aimed at describing the trajectory of treatment effects over time; however, they will not serve as an additional confirmatory primary endpoint.

Missing data for the primary endpoint will be handled under a mixed-effects model framework based on the missing-at-random (MAR) assumption. Multiple imputation will be used as a prespecified sensitivity analysis to assess the robustness of the primary results.

For non-primary outcome measures, repeated-measure mixed-effects models will be used to analyze continuous variables, as appropriate. Continuous variables measured only once after baseline will be analyzed using analysis of covariance (ANCOVA), adjusted for baseline values, where appropriate. Categorical variables will be analyzed using chi-square tests, Fisher’s exact test, or logistic regression, as appropriate. For non-primary outcome measures, formal correction for multiple comparisons is not currently planned; therefore, all such analyses should be considered secondary or exploratory, interpreted with caution, and not treated as confirmatory evidence.

The primary non-inferiority analysis will use a one-sided *α* = 0.025; all other analyses will use two-sided tests, with *p* < 0.05 indicating statistical significance. All statistical analyses will be performed using IBM SPSS Statistics version 24.0.

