### Study design

2.1

This trial is a prospective, multicenter, double-arm, assessor-blinded, parallel-group, randomized controlled non-inferioritytrial. Eligible participants will be randomized 1:1 to either Music Therapy Group (MTG) or Conventional Pulmonary Rehabilitation Group (CPRG). Both groups will receive interventions at a frequency of 60 min per session, 3 times per week, for 6 weeks.

The primary outcome is the between-group difference change in the 6-min walk distance (6MWD) from baseline (T0) to Week 6 (T6), which will be evaluated under a non-inferiority framework. Non-primary outcomes include dyspnea severity, respiratory health status, pulmonary function, adherence-related measures, arterial blood gas parameters, Traditional Chinese Medicine (TCM) syndrome assessment, patient satisfaction, adverse events, and the number of acute exacerbations of COPD (AECOPD) during the 1-year post-intervention follow-up.

The 6MWD, the COPD Assessment Test (CAT), and the modified Medical Research Council (mMRC) dyspnea scale will be measured at baseline (T0), weekly during the intervention (T1–T5), and post-intervention (T6). Pulmonary function and arterial blood gas analysis will be measured at T0 and T6. Adherence-related measures and adverse events will be recorded throughout the intervention period. AECOPD outcomes will be recorded throughout the 1-year follow-up. This study will adhere to the Consolidated Standards of Reporting Trials (CONSORT) statement for non-drug trials. The trial flowchart is shown in Figure 1, and assessment plan for primary and secondary outcome measures is shown in Table 1.

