### Participants and recruitment

2.2

Recruitment for this trial will be conducted at four participating centers in China, including the Fifth Affiliated Hospital of Guangzhou Medical University, Anshun People’s Hospital, Xixiu District People’s Hospital of Anshun, and Pingba District People’s Hospital of Anshun. The study protocol has been approved by the Ethics Committees of all participating centers (Ethics Review Numbers: GYWY-L2024-96, ASSRMYYLL-20240168, 2025-EC-001, 20,250,014). Clinical staff at each subcenter will pre-screen and potential participants. To standardize procedures and advance recruitment efforts, the lead unit’s research team will hold monthly in-person or online meetings with all of the subcenter clinical members. Interested patients who meet preliminary criteria will be invited to the hospital. Researchers will provide an in-person study introduction and address patient inquiries.

Voluntarily participating patients will undergo further medical history interviews and pulmonary function tests to confirm final eligibility. After providing written informed consent, eligible patients will complete baseline assessments. The initial intervention must be administered within 14 days following the baseline assessment.

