### Randomization and blinding

2.3

This study employed a centralized randomization system with stratified randomization by research center and variable block lengths. A computer-generated random sequence assigned eligible participants in a 1:1 ratio to either the music therapy group or the conventional pulmonary rehabilitation group. Each stratum contained 3 to 10 participants per group to ensure balanced group sizes. To conceal allocation, assignments will be placed in sequentially numbered, opaque, tamper-evident envelopes. The site coordinator will open the envelope only after the participant completes consent and baseline assessments, immediately before the first session.

Due to the nature of the interventions, participants and therapists is not blinded, while staff responsible for outcome assessment and statistical analysis will be blinded.

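### Randomization is stratified by center and the primary model adjusts for it, but center is not named in the ANCOVA or categorical analyses of non-primary outcomes: a small, conditional loss of precision or power

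*Protocol article*

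**What the plan says.** All references are to the protocol article.

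- **Design (2.2, 2.3).** "Recruitment for this trial will be conducted at four participating centers in China", and the allocation uses "stratified randomization by research center" with variable block lengths, 1:1.
- **Primary model (2.7).** The terms are listed: "Treatment group, visit time, the interaction term between group and time, study center, and baseline 6MWD will be treated as fixed effects".
- **Non-primary continuous outcomes (2.7).** Outcomes with repeated measurements go to mixed models whose terms are not listed. For the others: "Continuous variables measured only once after baseline will be analyzed using analysis of covariance (ANCOVA), adjusted for baseline values, where appropriate". By Table 1 these are FEV1, FVC and FEV1/FVC (key secondary) and PaO2, PaCO2 and the TCM Syndrome Scale (exploratory), all measured at T0 and T6.
- **Non-primary categorical outcomes (2.7).** "Categorical variables will be analyzed using chi-square tests"; the sentence goes on to allow Fisher's exact test or logistic regression, as appropriate. No stratification or covariate is named.
- **Status (2.7).** Non-primary analyses are two-sided at 0.05, without multiplicity correction, and are declared not confirmatory. The section opens by referring all analyses to a pre-specified SAP, which is not shown.

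**The concern.** Blocking within center makes the two arms nearly equal in every center, so differences between centers largely cancel from the treatment contrast. A model without center does not know this. It leaves the center differences in the residual variance, so the standard error describes a less precise comparison than the one that was run. The result is a conservative test and, for a continuous outcome, an interval wider than it needs to be.

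Section 2.7 names the adjustment for both the primary model and the non-primary ANCOVA, and the two differ on the stratification factor. For categorical data, plain chi-square and Fisher's exact tests ignore the design altogether.

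What is at stake is modest: some precision for spirometry, blood gases and the TCM scale, and some power for binary outcomes, in a trial of 76 with 60 expected to be evaluable.

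**Working it through.** **Inputs.** From the documents: four centers, 1:1 allocation blocked within center, 60 evaluable of 76 randomized, two-sided 0.05. Not in the documents, so assumed: the share ρ of outcome variance lying between centers after baseline adjustment, taken as 0, 0.02, 0.05, 0.10 and 0.20.

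**The plan's own figure.** The plan gives no figure for the non-primary analyses. The sample sizes used here do reproduce. The pooled variance is (36.6² + 32.3²)/2 = 1191.4, so SD = 34.52 m. Then n per arm = 2 × (1.960 + 0.842)² × 1191.4 / 25² = 29.9, or 30 per arm and 60 in total. With 20% dropout, 30/0.8 = 37.5, or 38 per arm and 76 in total.

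**ANCOVA, by formula.** With four equal centers and arms balanced within center, the expected residual variance without center, relative to that with center, is

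1 + [(3N/4)/(N − 3)] × ρ/(1 − ρ).

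For N = 76 the bracket is 57/73 = 0.781.

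- ρ = 0.02: 1 + 0.781 × 0.0204 = 1.016; square root 1.008
- ρ = 0.05: 1 + 0.781 × 0.0526 = 1.041; square root 1.020
- ρ = 0.10: 1 + 0.781 × 0.1111 = 1.087; square root 1.042
- ρ = 0.20: 1 + 0.781 × 0.25 = 1.195; square root 1.093

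The square root is the approximate ratio of standard errors. The three degrees of freedom that center uses barely change the critical value (1.993 on 73 df, 1.994 on 70).

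**ANCOVA, by simulation.** Four equal centers, permuted blocks of 2 and 4 within center, baseline-adjusted ANCOVA with and without center, 4,000 runs per scenario. The Monte Carlo standard error of a 5% rejection rate is √(0.05 × 0.95/4000) = 0.35 points. Ranges cover N = 60 and N = 76.

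| ρ (assumed) | CI width without / with center | Type I error without center | Power lost without center |
|---|---|---|---|
| 0 | 0.997–0.998 | 4.7–4.8% | 0–0.1 points |
| 0.02 | 1.005–1.006 | 5.0–5.2% | 0.1–0.2 points |
| 0.05 | 1.016–1.018 | 4.0–4.4% | 0.9–1.3 points |
| 0.10 | 1.04 | 4.1–4.3% | 2.3–2.4 points |
| 0.20 | 1.09 | 2.8–3.8% | 4.4–4.7 points |

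The power columns used standardized effects of 0.74 (N = 60) and 0.65 (N = 76), which give about 79% power when center has no effect. At ρ = 0 and 0.02 the type I error cannot be told apart from 5%. Formula and simulation agree closely.

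**Equal centers.** If a stratum in section 2.3 is a center, its limit of 10 per group means that, with 38 per group over four centers, none can fall below 38 − 30 = 8 per group. Near-equal centers is then a fair assumption.

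**Binary outcomes.** Expected-data logistic fits at N = 76, with an assumed within-center log odds ratio of 0.8:

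| Center SD on logit scale (assumed) | Without center: log OR (SE), z | With center: log OR (SE), z |
|---|---|---|
| 0.5 | 0.755 (0.476), 1.59 | 0.800 (0.491), 1.63 |
| 1.0 | 0.649 (0.471), 1.38 | 0.800 (0.529), 1.51 |

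In the second row the odds ratio moves from exp(0.800) = 2.23 to exp(0.649) = 1.91. The 95% interval on the log scale is 2 × 1.96 × 0.471 = 1.85 wide without center and 2 × 1.96 × 0.529 = 2.07 wide with it. Omitting center shrinks the estimate and lowers z, but narrows the interval.

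**The case against.** The strongest reply is that silence is not exclusion. Section 2.7 does not say that center is left out, it qualifies the ANCOVA with an appropriateness clause, and it hands all analyses to an SAP that is not shown. Full covariate lists for secondary models usually belong there. This stands as a limit on the claim: one cannot say that the trial will omit center. It does not dispose of the point, because the article itself names the ANCOVA adjustment and names two tests that cannot carry the stratification factor. Following that text as written gives the weaker analysis.

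Logistic regression is already among the listed methods and could carry a center term. That also stands, so the categorical part concerns only an unadjusted logistic model and the chi-square and Fisher options.

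The size rests on an assumption. A stable center offset in equipment or scoring would affect T0 and T6 alike, so baseline adjustment would absorb part of it. Section 2.6 also plans evaluator training and the same evaluator for each participant's tests. The true share may therefore lie at the low end, where the loss is 2% of width or less. A reader might infer that each hospital measures with its own equipment; that is plausible, but the documents do not say so.

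Finally, nothing confirmatory depends on these analyses. That is correct and sets the severity.

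**Conclusion.** The point holds as a minor one. Center is the stratification factor and sits in the primary model, but is not named for the non-primary ANCOVA or categorical analyses. If it is omitted and is prognostic after baseline adjustment, ANCOVA intervals are about 0.5–2% too wide at a center share of 2–5%, 4% at 10% and 9% at 20%. Type I error falls below 5% from a share of about 5% upward. With no center effect there is no loss. These figures assume four equal centers and a center share that the documents do not give.

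Three stronger readings are not supported:

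- **Invalid or anti-conservative tests.** Omitting center did not raise the type I error above 5% beyond simulation error in any scenario; any departure is on the conservative side.
- **Too-wide intervals for binary outcomes.** In logistic regression the interval narrows. The odds ratio without center is a population-average quantity closer to 1, and its test has somewhat less power.
- **A threat to the primary result.** The primary model already includes center, so the non-inferiority conclusion is untouched.

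**What to change.** Add to section 2.7, or confirm in the SAP, wording to this effect:

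*The ANCOVA, mixed and logistic models for non-primary outcomes include study center as a fixed effect, as in the primary model. Categorical comparisons use a center-stratified Mantel-Haenszel method where counts allow, with Fisher's exact test as the fallback for sparse cells.*

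The fallback should have a stated trigger, because each center contributes only about 38/4 = 9.5 participants per arm and event counts by center may be small.

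The cost is a sentence or two and three degrees of freedom (73 to 70 in an ANCOVA at N = 76, 57 to 54 at N = 60). Center is known for every participant from the randomization, so no new data are needed. If center proves irrelevant, including it widens the interval by only 0.2–0.3% (1/0.998 to 1/0.997). Sample size, margin and primary analysis do not change.

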### Sample size calculation

2.8

This study is designed as a non-inferiority, and the sample size was estimated based on the between-group difference in the change in 6MWD from baseline to week 6. For the primary endpoint, the non-inferiority margin was prespecified as 25 m. This margin was established as a conservative and clinically meaningful threshold, based on previous studies indicating that the minimum clinically important difference (MID) in the 6MWD for patients with COPD is approximately 25–26 meters (17, 18). The primary hypothesis of this study is the non-inferiority of the difference in changes in 6MWD between the two groups. Secondary outcomes will be analyzed as secondary or exploratory endpoints and interpreted with caution. Given the current lack of directly comparable studies on music-guided breathing training combined with singing techniques, this study referenced standard deviation estimates of 6MWD changes (36.6 m and 32.3 m) from a similar rehabilitation intervention study as a basis for parameter selection. Under the conditions of a one-sided *α* = 0.025 and 80% power, the estimated required sample size was 60 participants (30 per group). Accounting for a 20% dropout rate, the final target sample size was set at 76 participants (38 per group).

## Discussion

3

Enhancing long-term patient adherence while maintaining the efficacy of rehabilitation remains a key challenge in pulmonary rehabilitation for COPD. This multicenter randomized controlled trial aims to evaluate an integrated intervention combining music-guided breathing training and singing techniques, and may provide evidence for the development of more engaging rehabilitation strategies.

COPD remains a major global health challenge and continues to place a heavy burden on patients, families, and healthcare systems (19, 20). Against this backdrop, optimizing disease management remains a key priority in both clinical and public health settings. Pulmonary rehabilitation (PR) remains the cornerstone of non-pharmacological treatment for COPD, effectively alleviating dyspnea and improving physical function and quality of life (4). Existing evidence indicates that pulmonary rehabilitation is one of the most cost-effective interventions for COPD (21, 22). A meta-analysis demonstrated that pulmonary rehabilitation reduces readmission rates after discharge from acute exacerbations of COPD, alleviates dyspnea, enhances exercise endurance, and improves quality of life (23). A clinical trial further revealed that long-term sustained pulmonary rehabilitation alleviates clinical symptoms and increases 5-year survival rates (24). Conventional pulmonary rehabilitation programs primarily focus on aerobic exercise and endurance training. Aerobic and endurance training significantly enhance exercise capacity by directly targeting peripheral muscles (25). Breathing training techniques such as abdominal breathing, pursed-lip breathing, and diaphragmatic breathing effectively coordinate respiratory muscle activity and optimize thoracoabdominal movement patterns, thereby alleviating dyspnea and pulmonary hyperinflation (8). However, conventional pulmonary rehabilitation—particularly respiratory muscle training and endurance training—often suffers from poor long-term patient adherence due to repetitive content and monotonous formats (6). Consequently, exploring novel interventions that combine engaging elements with core rehabilitation principles has become a research priority.

The value of music therapy in pulmonary rehabilitation for COPD has received increasing attention in recent years (26–28). Previous studies have confirmed that group music therapy can reduce acute exacerbations and improve lung function in patients with COPD (29, 30), while a meta-analysis also indicates potential benefits in enhancing exercise tolerance and quality of life (31). Additionally, clinical studies report that music-based interventions may help patients overcome breathing difficulties and fatigue fears associated with physical activity, thereby improving their motivation to participate in pulmonary rehabilitation (32, 33). Based on this, this trial integrates music therapy with breathing exercises, using musical rhythms to guide COPD patients in performing diaphragmatic breathing and pursed-lip breathing. This approach aims to preserve the core therapeutic principles of breathing exercises while enhancing the engagement and acceptability of the intervention.

Singing is another commonly used form of music therapy. Vocal training helps patients establish more efficient breathing patterns, strengthen respiratory muscles, and improve hyperinflation and dyspnea (34–36), while the process is typically more relaxed and enjoyable (37). A recent study also found that consistent 10-week vocal training improved the 6-min walk distance in COPD patients, with efficacy comparable to conventional exercise training (38). However, previous music therapy studies predominantly focused on single interventions modalities. Based on this, the trial aims to combine music-guided breathing training with singing, to evaluate whether this integrated rehabilitation model can provide a more engaging intervention experience for COPD patients while maintaining therapeutic benefits.

Although the primary endpoint of this study is the change in 6MWD from baseline to Week 6, the repeated measurement of 6MWD during the intervention period was one of the study’s key methodological features. Compared with designs that assess outcomes only before and after the intervention, this approach allows for a more detailed description of the trajectory of functional outcomes over time. For secondary outcomes, this trial aims to investigate whether a music-based intervention, compared with conventional pulmonary rehabilitation, results in different patterns of change in outcomes related to dyspnea, health status, and physiological parameters. In particular, this study may provide further insights into the responsiveness of patient-reported outcomes (such as mMRC dyspnea scores and CAT scores) and physiological parameters (including pulmonary function and arterial blood gas parameters).

This protocol also features several design elements that may enhance its methodological value. First, this protocol uses an active-control design, with both groups receiving structured rehabilitation interventions of identical frequency and duration. This may improve comparability between groups and reduces the influence of nonspecific factors such as attention and social interaction. Second, the multicenter study framework and the use of standardized intervention and assessment procedures may help enhance the study’s feasibility, consistency, and robustness across different clinical settings.

This trial also has several limitations. First, due to the nature of the intervention, blinding of participants and intervention providers was not feasible, potentially introducing bias. However, the use of a highly objective primary outcome measure (6MWD) and strict assessor blinding maximized control over measurement bias. Second, the distribution of study centers has not yet covered more diverse geographic and economic regions nationwide, potentially limiting the generalizability of findings to some extent. Third, although repeated 6MWD assessments may provide richer longitudinal data, they may also increase the burden on participants and the complexity of study implementation. Another limitation is that, although the two groups were matched in terms of frequency, duration, therapist contact time, and monitoring framework, there was a design difference in their exercise patterns. The intervention group underwent music-guided breathing training, vocal exercises, and singing, whereas the control group underwent standardized exercise training. Therefore, the study results should be viewed as a comparison between two rehabilitation modalities, and this design difference should be taken into account when interpreting the findings.

The intervention evaluated in this study protocol is an integrated rehabilitation model, rather than a simple add-on to conventional breathing training. Its potential value lies in combining breathing training with structured, music-guided training modalities, which may support respiratory control and task engagement in patients with COPD. Therefore, this study aims to evaluate whether this integrated model is at least as effective as traditional pulmonary rehabilitation training in improving the 6-min walk distance, and to provide exploratory information on adherence, feasibility, satisfaction, and patient-reported outcomes. The results of this study may provide preliminary evidence for further evaluation of music-guided breathing training combined with singing as a viable adjunct in COPD rehabilitation.
